### Adverse events

Adverse events for the study will be classified as low risk (evidence of high level of distress or concerns for possible risk of harm to individual or safeguarding risk) or high risk (clear evidence of immediate and serious risk to participant’s life or child welfare). Such events will be detected through participant interviews, direct contact (telephone or email) from participant to researchers or trial manager, or through red flag alerts on specific online assessment items. For low-risk events participants will be sent a supportive email signposting them to relevant third sector and NHS support options. For high-risk events the researcher will contact relevant services. In case of immediate risk to life the researcher will contact 999. For immediate and/or serious child welfare risk social services safeguarding teams will be contacted. All risk events will be reported and recorded. Events will be discussed with the supervising clinician. High risk events will be reviewed by TSC chair to evaluate possible relatedness. If related the CI will be unblinded and the sponsor, ethics committee and funder will be informed. Risk events will be reviewed by the DMEC for both trial arms.

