### Confidentiality

Participant data will be shared with third parties (social services/clinical teams/emergency services) only when serious and/or immediate harm to themselves or others is likely, or a safeguarding concern is raised. Participants will consent to information being shared in this way when they complete the full trial consent form. Participants’ personal data will be stored on Lancaster Teams and on the secure cloud-hosted REDCap server, with access only to delegated trial team members. Baseline and follow-up assessments will be stored on the secure cloud-hosted REDCap server. Responses to the feedback survey will be stored on a secure Lancaster Qualtrics account with access only to delegated, unblinded trial team members.

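### Child-welfare risk has two thresholds within the adverse-events section, and the stated relatedness review follows the narrower one

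*Protocol article*

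**What the plan says.** The Adverse events section of the protocol article has two grades.

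- **Low risk** is "evidence of high level of distress or concerns for possible risk of harm to individual or safeguarding risk". The response is: "For low-risk events participants will be sent a supportive email signposting them to relevant third sector and NHS support options".
- **High risk** needs "clear evidence of immediate and serious risk", applied to the participant's life or to child welfare. The response is: "For high-risk events the researcher will contact relevant services".

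Two more specific action sentences follow. For life: "In case of immediate risk to life the researcher will contact 999". For the child: "For immediate and/or serious child welfare risk social services safeguarding teams will be contacted".

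The section then sets out oversight. Every risk event is recorded, discussed with the supervising clinician and reviewed by the DMEC in both arms. Only high-risk events are said to go to the TSC chair for a judgement on relatedness. Unblinding of the chief investigator and notification of the sponsor, ethics committee and funder depend on that judgement.

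The Confidentiality section allows participant data to go to third parties "only when serious and/or immediate harm to themselves or others is likely, or a safeguarding concern is raised", and says that participants consent to this.

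**The concern.** The grade joins the two conditions with *and*; the child-welfare action sentence joins the same two with *and/or*. An event that meets one condition but not the other falls between them: it is to be referred to safeguarding teams, yet it does not qualify as high risk.

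The grade also decides who assesses relatedness. If the text is followed literally, an event serious enough for referral to social services may never be put to the TSC chair, and the external notifications that depend on the chair's judgement would not be triggered. Two researchers who rely on different sentences could also grade the same disclosure differently.

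**Working it through.** The article gives no figure to reproduce here, so the check sets the rules side by side.

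**Inputs.** The grade definitions, the two action sentences and the relatedness rule come from Adverse events. The data-sharing rule comes from Confidentiality.

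**Child welfare.** Two conditions, each met or not, give 2 × 2 = 4 combinations.

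| Immediate | Serious | Meets high-risk definition (both) | Referral sentence applies (either) | TSC chair review stated |
|---|---|---|---|---|
| yes | yes | yes | yes | yes |
| no | yes | no | yes | no |
| yes | no | no | yes | no |
| no | no | no | no | no |

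The first and last rows agree. The two middle rows do not: referral applies, the high-risk definition is not met, and no relatedness review is stated. That is 2 of 4.

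**Grade of the middle rows.** With only two grades, these events fall to low risk by default. The fit is not exact, because low risk is worded as "concerns for possible risk of harm to individual or safeguarding risk" whereas high risk asks for clear evidence. A clearly evidenced, serious but non-immediate event may fit neither definition well. Whether it is graded low or left ungraded, the relatedness step is not stated for it.

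**Risk to the participant's own life.** The action sentence here is triggered by immediacy alone. A serious but non-immediate risk to life fails the high-risk definition, and no wider action sentence picks it up. No relatedness review is stated for it either, but there is no second prescribed response. The mismatch between grade and referral is therefore shown for child welfare only.

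**Safeguarding.** Adverse events places safeguarding risk in the low-risk class, with the email as response. Confidentiality names a safeguarding concern as sufficient ground for sharing data. The first prescribes a response and the second sets a limit on disclosure. The two thresholds differ, but they do not order two different actions.

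**The case against.** The best defence is that the action sentences only elaborate the high-risk branch. The general rule that services are contacted for high-risk events is followed at once by which services: emergency services for life, safeguarding teams for the child. On that reading *and/or* is loose drafting, and no event below high risk is referred. The text allows this reading, but the section would still state two thresholds for the same thing, with nothing to tell the researcher which governs.

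It can also be said that this is a condensed article and that a fuller risk procedure may settle the matter. That would excuse missing detail. Here, sentences that are present disagree.

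Other parts of the defence stand, and they rule out stronger conclusions that a reader might infer:

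- *That the responses are opposite.* A signposting email and a referral can both be carried out, and nothing forbids referring a low-risk event.
- *That Confidentiality gives a conflicting instruction.* It says when sharing is allowed, and a permission may be wider than a duty.
- *That all serious but non-immediate events, including parental self-harm, are pulled two ways.* The wider action sentence covers child welfare only.
- *That such events escape oversight.* They are recorded, discussed with the supervising clinician and reviewed by the DMEC. Under Data monitoring, the DMEC can see unblinded data and make safety recommendations to the TSC, and weekly operational meetings cover risk issues.
- *That a comparison between arms is distorted.* The article nowhere says that the DMEC compares counts of high-risk events.
- *That every child-welfare disclosure is affected.* Events meeting both conditions or neither are handled consistently.

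**Conclusion.** The point holds in a limited form. Adverse events uses a narrower threshold to grade child-welfare risk than to refer it, and attaches the relatedness review and its onward reporting to the narrower one. Events in two of the four combinations can be referred to safeguarding teams without a stated relatedness review by the TSC chair. The different placing of safeguarding matters in Adverse events and Confidentiality is a secondary mismatch of thresholds.

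The size in events is unknown, because the article gives neither a rate nor a count. The conclusion assumes that the sentences are applied as written and that no separate procedure overrides them. It implies nothing about whether any event has in fact been misgraded.

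The primary outcome and its analysis are untouched. The matter is nevertheless one of child safety and safety reporting, and the Recruitment section describes enrolment as still open, until 30 November 2025. It should be corrected promptly.

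**What to change.** 1. Reconcile the high-risk definition, the child-welfare action sentence and the Confidentiality wording so that one threshold runs through all three, and give safeguarding risk or concern one consistent place. The trial's safeguarding leads should decide which wording stands; this review takes no position on it.
2. State which review route, including relatedness, follows when an event is referred to outside services. Reconciliation does not in itself require every outside contact to go to the TSC chair; it requires the route to be explicit.
3. Check the event log for child-welfare events that were referred but not graded high risk, and establish whether relatedness was assessed. A check is enough unless it finds affected events.

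The cost is a wording amendment, with the sponsor review and ethics committee approval that the Protocol amendments section already requires, possibly a matching change to the consent text, and one pass through the event log, whose size the article does not give.

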### Ethics and auditing

Although no specific audits are planned, these can be requested by NIHR, TSC, DMEC and sponsor as well as other study partners.

## Ethics and dissemination

### Research ethics approval

This study has received NHS REC approval (West Midlands – Solihull Research Ethics Committee 22/WM/0200).

### Protocol amendments

Any protocol amendments will be reviewed by the Sponsor. These will also be shared with the Research Ethics Committee (REC) for approval prior to implementation.

### Consent

Participants must provide their consent to take part in the study and will be asked for their consent up to four occasions. Firstly, participants will register their interest to participate and consent to be contacted using MS Forms, which is accessible from the trial webpage www.lancaster.ac.uk/health-and-medicine/research/spectrum/research/ibpi/. The consent to contact form provides consent for their data to be stored in line with UK General Data Protection Regulation (GDPR) laws and the Data Protection Act 2018. Data includes phone number, email address, and postal address. Following an initial screening call if deemed potentially eligible, the researcher completing the screening call will send a link to the full trial consent form (on the cloud-hosted REDCap server). Completion of the full trial consent form provides both consent to participate in the full trial as well as consent to be invited to participate in the qualitative aspect of the trial for those randomised to the IBPI + TAU arm. Invites to feedback surveys will occur following a participant’s completion of their 24-week assessment, or if incomplete, four weeks after the assessment window has opened, and all prompts to complete the assessment have been sent. Participants will be sent a link via email to Qualtrics to complete the consent form. Once complete they will be directed to the feedback survey. A sample of participants who have completed their survey (up to *n* = 15–20) will be invited to a feedback interview via email. The email will contain a link to complete the feedback interview consent form which will be hosted on Qualtrics. Participants will not be invited to complete a feedback survey or feedback interview if they have not agreed to be contacted for the qualitative aspect of the trial, or if they have moved into the 48-week post randomisation assessment window.

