### Secondary objectives

1. To determine the clinical effectiveness of IBPI on the secondary outcomes:

i)Child behavioural and emotional problems at 48 weeks, measured using the SDQ.ii)Parenting competence, confidence, and stress at 24 and 48 weeks, measured using the Parenting Scale (PS [30]), the Parenting Sense of Competency Scale (PSOCS [31]), and the Parenting Stress Index Short Form (PSI-4-SF [32]).iii)Parental mood (self-rated mania and depression) at 24 and 48 weeks, measured using the Internal States Scale (ISS [33]), the Centre for Epidemiologic Studies Depression Scale (CES-D [34, 35]), the Altman Self Rating Mania Scale (ASRM [36], the Generalized Anxiety Disorder Scale (GAD-7 [37]), and the Life Chart Method – Retrospective (LCM-r, adapted from the NIMH-LIFE [38]).iv)Family coherence at 24 and 48 weeks, measured using the Confusion, Hubbub, and Order Scale (CHAOS [39]).

2. To determine the cost effectiveness of IBPI:

i)The primary economic objective is to compare the cost-utility of IBPI + TAU vs. TAU assessed at 24 weeks with effects measured in terms of quality-adjusted life years (QALYs) generated from the Child Health Utility 9 Dimension measure of health-related quality of life (CHU9D [40]).ii)The secondary economic objectives include:

Cost-utility analysis using QALYs at 48 weeks.Cost-utility analysis using QALYs at 24 and 48 weeks including costs and effects for the parent in addition to the child, with QALYs for the parent measured using the EQ-5D-3 L measure of health-related quality of life [41].Cost-effectiveness analysis using the primary clinical outcome measure (SDQ) at 24 and 48 weeks.

3. Obtain views of IBPI recipients on their experiences of IBPI:

i)A feedback survey will be sent to participants in the IBPI + TAU arm after 24-weeks to determine their levels of intervention use, and, if applicable, their opinions of the website. Only participants who have consented to be contacted for the qualitative study will be sent the survey.ii)Qualitative interviews will be conducted with a sub-sample of participants who have completed the feedback survey. The sub-sample will be based on (i) stratification variables and (ii) levels of intervention use (determined by survey responses). The topic guide for these interviews will include questions about participants’ perceptions of what has changed following IBPI, the factors which influenced their level of engagement, and their recommendations for improvement.

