#### Feedback survey

To supplement the feedback interviews, all participants in the intervention arm who have consented to be contacted for the qualitative aspect of the trial will be sent a feedback survey. The survey will combine multiple choice questions with open questions where participants can provide free text responses. The feedback survey will establish participants’ level of intervention use and, if relevant, will ask participants their opinion of the intervention, and whether they experienced any changes from using the intervention.

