#### Feedback interviews

A subset of participants (*n* = 15–20) from the IBPI + TAU arm who have completed the feedback survey, will be selected with maximum variance sampling on (i) stratification factors and (ii) levels of intervention use (determined by responses to the feedback survey) to participate in a feedback interview. The purpose of this interview will be to gain a more in-depth understanding of participant experiences with the IBPI website, such as what worked well, what still needs to be improved, and why. The feedback interview will also explore participants’ appraisal of it, what they have learned from the intervention, and patterns of website use. Importantly, this interview will also ask participants to share their perceptions of what has changed for them and their child because of their completion of the intervention and will look to identify any barriers/facilitators to engagement. The topic guide for these interviews will be co-developed with our SURG.

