### Blinding

Participants will not be blinded to their intervention and will self-complete all outcome measures. Researchers involved in supporting follow-up assessments will be blind to treatment allocation as will the Chief Investigator, except where there is immediate risk of harm to a participant and this needs to be broken for safety reasons. The senior health economist will be blinded to trial allocation for analysis. Trial statisticians and the trial health economist analysing the data will not be blinded. The Trial Manager, and Trial Support Officer at YTU can view the group allocation but are not party to the unblinded results. Group allocation will be communicated via email (through the REDCap system) to the randomisation inbox to which only the Trial Manager and Project Administrator will have access. This is to monitor adherence to the algorithm for randomisation and allow for a mechanism of informing participants of their group allocation. Any queries regarding the intervention can then be discussed with the Trial Manager to ensure blind breaks do not occur with other blinded researchers. Participants will be reminded not to unblind researchers at each assessment point. Should an unblinding occur, subsequent assessment support for that participant will be conducted by an alternative researcher. All blind breaks will be reported to the DMEC and the TSC.

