### Optimising retention

Attrition is a key challenge faced by online trials [66]. Our retention strategy has been informed by previous studies run by Lancaster University, our team [23, 67], and a recent meta-analysis [68]. To maximise retention in the current study we will:

Include an explanation in the Participant Information Sheet describing why data completion at follow-up is important.Only randomise participants once they have completed the measures at baseline.Send participants scheduled email and telephone reminders to prompt engagement with the intervention and with each assessment point, based on previously successful strategies [69]. If participants still do not complete measures, we will send the measures in the post to be completed by pen and paper.Pay participants for completing questionnaires at each assessment point: £40 for completing the SCID and baseline measures, £10 for completing 24-week measures, £10 for completing 48-week measures, £5 for completing the feedback survey and £40 for those who attend a feedback interview. There is some evidence to suggest that paying participants improves retention [65, 70].Allow participants who may be unable to complete all follow-up measures to only complete some of them, with an emphasis on the primary outcome measure (SDQ).Allow participants to complete assessments at times and locations of their choosing by using online self-report measures.We will review attrition by key characteristics throughout the trial to identify patterns and bring in strategies that might support specific groups to continue to take part.

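### The IBPI-only feedback survey can be sent while a participant's primary 24-week SDQ is still outstanding

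*Protocol article*

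**What the plan says.** **Who is contacted.** Under Secondary objectives: "A feedback survey will be sent to participants in the IBPI + TAU arm after 24-weeks to determine their levels of intervention use". The Feedback survey section adds that "all participants in the intervention arm who have consented to be contacted for the qualitative aspect of the trial will be sent a feedback survey". Feedback interviews follow for 15–20 IBPI parents who have completed the survey. TAU has no counterpart to either.

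**What they are asked.** The survey covers level of use, opinion of the site and "whether they experienced any changes from using the intervention". For the interview, "this interview will also ask participants to share their perceptions of what has changed for them and their child".

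**When.** The Consent section ties the survey invitation to completion of the 24-week assessment, with a fallback: "or if incomplete, four weeks after the assessment window has opened, and all prompts to complete the assessment have been sent". Invitations are barred for people who did not agree to qualitative contact, "or if they have moved into the 48-week post randomisation assessment window".

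**Who rates the outcomes.** The Blinding section states: "Participants will not be blinded to their intervention and will self-complete all outcome measures". The primary outcome is the index child's SDQ total at 24 weeks.

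**Late returns and payments.** Optimising retention provides for paper forms to be posted to parents who have still not completed their measures. It pays £10 at 24 weeks and £10 at 48 weeks in both arms, plus £5 for the survey and £40 for the interview. The article does not say when 24-week collection closes.

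**The concern.** In an open-label trial with parent-rated outcomes, research contact before an outcome should be the same in both arms. The fallback breaks that rule for the primary outcome. It is triggered exactly when the 24-week assessment is incomplete, and it then asks IBPI parents, and only them, about change due to the intervention. A parent who answers the survey and then returns the SDQ has been led to think about benefit, or its absence, just before scoring the child. If this altered the score, the 24-week difference would contain something other than the effect of IBPI. No analysis could separate the two afterwards, because no TAU parent receives the contact.

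The same asymmetry applies by design at 48 weeks. All qualitative invitations precede the 48-week window, so the 48-week SDQ, the other parent-rated secondary outcomes and the 48-week economic outcomes follow an IBPI-only contact.

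**Working it through.** This is mainly a question of the order of events. Arithmetic only sets the scale.

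**1. Order of events for the 24-week SDQ**
- *IBPI parent who completes the assessment:* SDQ first, then the invitation. The primary outcome is not exposed.
- *IBPI parent still incomplete four weeks after the window opens, all prompts sent:* invitation first. Any SDQ that arrives later follows the invitation.
- *TAU parent, on time or late:* never invited.

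Only the second path exposes the primary outcome. It needs a late SDQ to be accepted. The posted paper form makes this possible and nothing in the article rules it out, but the article does not state it either.

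**2. Arm size**

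The plan's figures reproduce. The adjusted SD is 6.46 × √(1 − 0.65²) = 4.909. A t-based calculation for a 2-point difference, 90% power and 5% two-sided gives 128 per arm, 256 in total. Then 256 / 0.90 = 284.4, against the stated 284. So 284 / 2 = 142 are randomised per arm, and 0.90 × 142 = 127.8, about 128, are expected to supply the 24-week SDQ.

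**3. How many are exposed before the primary SDQ**

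Not derivable. The 142 − 128 = 14 participants per arm not retained are people with no 24-week SDQ, not people with a late one. The article gives no count of late returns.

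**4. Scale, by assumption only**

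If L exposed parents shift their rating by d points on average, the observed IBPI mean moves by L × d / 128.
- One parent, 1 point: 1 / 128 = 0.008 points.
- L = 7, d = 0.5: 3.5 / 128 = 0.03 points.
- L = 14, d = 2: 28 / 128 = 0.22 points.

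Neither L nor d comes from the documents. The range shows only that a handful of late returns cannot move the mean far against the 2-point target.

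**5. The 48-week contact**

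- Interview share: 15 / 142 = 10.6% to 20 / 142 = 14.1% of the arm.
- Maximum follow-up payments: TAU £10 + £10 = £20; IBPI survey completer £20 + £5 = £25; IBPI interviewee £25 + £40 = £65.

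The survey reaches only those who agreed to qualitative contact. The Table 1 footnote expects it to start only after the internal pilot. The number surveyed is therefore not known.

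**6. Room to delay**

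Assuming the windows open at weeks 24 and 48, the fallback fires at week 28. That leaves 48 − 28 = 20 weeks in which an invitation can still be sent under the existing rule.

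**The case against.** The best defence is that the primary outcome is already protected for nearly everyone. The normal sequence puts the SDQ first, and the fallback waits both for four weeks and for every prompt to have been used, which may include the posted form. An affected parent would have to ignore all prompts, open a separate link, consent again, and only then return the SDQ. The closing date for 24-week data may be fixed in the full protocol or SAP. All this stands as an argument that the number is small. It does not show that the number is zero, and the rule as written permits the sequence.

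A process evaluation of IBPI also has no natural TAU version. Moving it beyond 48 weeks would cost recall: the feasibility data put the end of use at 3–4 months for over 95% of participants. This stands, and it is why the 48-week part calls for reporting and not for a change of design.

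A reader might infer more than the documents support:
- **That bias favours IBPI.** The survey asks whether changes occurred, and the interview also asks about barriers and what needs improving. Low engagement in the feasibility study makes neutral or negative answers just as plausible.
- **That payments differ by £65 to £20 across the arms.** This holds only for the 15–20 interviewees. For other survey completers it is £25 to £20.
- **That the survey newly sends lapsed users back to the site.** Reminders to use the intervention are already planned under Optimising retention.

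**Conclusion.** The point holds in a limited form. The fallback rule allows an arm-specific prompt about change to precede the self-rated primary outcome, in the IBPI arm only. It rests on one inference: that a 24-week SDQ arriving after the invitation would be accepted. The number affected is not stated and is probably small. No size or direction of bias can be derived from the documents, and they do not support the conclusion that the primary comparison is materially biased. The rule still merits changing, because the exposure is avoidable at almost no cost.

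For the 48-week secondary and economic outcomes the asymmetry is certain in timing but unknown in effect. It does not invalidate those results. It is a feature of the design that their report should disclose.

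**What to change.** 1. Replace the fallback in the Consent section. Send no feedback survey or interview invitation until that participant's 24-week SDQ has been received, or 24-week collection has been formally closed for them, with the closing point stated. This needs a small amendment and a changed invitation trigger. Its cost is a short delay for some surveys, which still fits before the 48-week bar.
2. For anyone already invited under the fallback, log the invitation date and the SDQ return date. Run a sensitivity analysis of the primary model that sets 24-week SDQs returned after the invitation to missing. Since that removes late returns from one arm only, repeat it with the same elapsed-time cut-off in both arms. The cost is two dates per participant and one extra analysis.
3. Report the survey, the interview and their payments (£5 for survey completers, plus £40 for the 15–20 interviewees) as an IBPI-only contact before the self-rated 48-week outcomes, with the numbers surveyed and interviewed.
4. Moving the qualitative contact after the 48-week assessment is optional. It would remove the 48-week asymmetry, but it lengthens recall, and a switch part-way would mix recall intervals within the qualitative sample.
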